#### Objective 3: impact of immunological status on outcomes in the shielding population

We will analyse data from tests already undertaken using anonymised population-scale linked EHR data sources including COVID-19 PCR data held in SAIL to make a broad assessment of immunity, immunological status, infections and antibiotic use. Immunological data will include:

Full blood count (FBC)—haemoglobin, platelets, white cell count, neutrophils, lymphocytes.Liver function test (LFT)—calculated globulin (total protein—albumin) Laboratory Information Management System (LIMS) test code B3062 (analysis by low and high calculated globulin).C reactive protein RP LIMS code B3023.Procalcitonin.Immunoglobulins (Ig)—IgG, IgA and IgM LIMS test code B3054.Serum electrophoresis.Glycated Haemoglobin.Renal function B5373.

We will also assess availability of less frequently tested immunological data:

Lymphocyte subsets—cluster of differentiation (CD): CD3, CD4, CD8, CD19 and CD56.Specific antibodies—haemophilus influenzae B, tetanus, pneumococcus and SARS-CoV-2.

We will invite people approached by postal questionnaire (2.2) to provide blood samples for linkage and extended analysis. We will collect dried blood spots from those who indicate consent on completed questionnaires (≥500 in each study arm). This self-administered test will be delivered and returned by post. We will identify a subgroup (50 in each study arm) and invite them to provide a liquid blood sample to investigate T-cell immunological responses. The liquid blood sample will be collected by a qualified health professional in the individual’s home.

#### Objective 4: behaviour, adherence and safety concerns of people who shielded

We will interview 40 people on the Shielded Persons List, their carers and/or household members, from those who agree to be contacted after completing the questionnaire (2.2) and then consent to take part. Interviews will be by telephone or online (eg, Zoom), recorded and transcribed with their consent. We will explore individual experiences during 2020, including behaviour, physical and mental health and also safety concerns (ie, an event or situation where something went wrong or not as expected while receiving or trying to receive healthcare).^37 38^ People with experience of shielding on our study team will codevelop the interview questions (online supplemental appendix 2). The study team will ensure interviewees reflect the range of people included in the shielding intervention in age, sex, health status, ethnic group and place of residence in Wales. We recognise that our sample may include individuals who have been bereaved and we will signpost to appropriate support.

10.1136/bmjopen-2021-059813.supp2Supplementary data

#### Objective 5: costs of the shielding intervention against its consequences

We will investigate implementation costs, including costs incurred in identifying those asked to shield and in managing shielding processes. We anticipate this will include costs of:

Developing and implementing algorithms (Public Health Wales; NHS Wales Shared Services; DHCW, formerly called National Wales Informatics Service) to identify defined categories of patients.Identifying additional patients within the NHS (via general practice registers, outpatient lists, etc).Managing and sending out shielding advice letters (NHS Wales Shared Services; NHS Wales Delivery Unit).Sharing lists and sending out support letters to shielded people from local authorities (NHS Wales Shared Services/Delivery Unit; Unitary Authorities across Wales).Sharing and sending messages to shielded people from supermarkets for prioritised delivery slots (NHS Wales Shared Services/Delivery Unit/Supermarkets).Providing food parcel deliveries/pharmacy prescription pick-ups and delivery (Unitary Authorities).

We will collect these data through interviews and documentary evidence from key informants at the organisations which collaborated in delivering this intervention. We will describe the consequences of shielding in terms of healthcare resource use based on patient-level linked data extracted from SAIL (and costed using published unit costs) and COVID-19-related morbidity and mortality and summarise net monetary benefits of shielding.

#### Objective 6: experiences and views of healthcare providers

We will interview 30 clinicians including general practitioners (GPs), primary care and community nurses, emergency department (ED), emergency ambulance and intensive care staff across locations in Wales. We will use vignettes developed from the interviews with the shielded population (objective 4) to understand challenges, particularly patient-reported safety concerns.^39^ Questions will include views on shielding, how it was implemented and how they felt it affected people including any health risks for patients (online supplemental appendix 3). Our public contributors will codevelop these tools. Interviews will be online or by telephone, recorded and transcribed with their consent.

10.1136/bmjopen-2021-059813.supp3Supplementary data

### Analysis

#### Objective 1: rationale for UK shielding

We will analyse data using framework analysis, recommended for use in policy and health services research.^40 41^ A senior qualitative researcher (AP) will lead a team of researchers and public contributors in reading and coding data for discussion and interpretation. Through this process, we will refine the logic model for the shielding intervention and understand the intentions of applying it—making explicit the hypothesised mechanisms for change, expected outcomes and risks.^32 33^ This model will guide interpretation of study findings including mechanism and outcomes data and dissemination.

#### Objective 2: effectiveness of shielding

We will analyse quantitative data following ‘intention to treat’ analysis principles. Our detailed statistical analysis plan, compliant with Swansea Trials Unit’s Standard Operating Procedure,^42^ will cover: descriptive summaries of study data and thematic categorisation; formal comparison of outcomes, adjusted for case mix and potential confounding factors; statistical modelling strategy underpinning comparisons, including conventions for dealing with missing data, selection of confounders; reporting of analyses. Modelling will use generalised linear and survival multilevel models for events, counts and time to events. Entry dates are based on the date identified as CEV (shielded cohort) or 20 March 2020 (matched cohort); 12-month follow-up data will be censored by death, or known date of migration from Wales.

There was considerable spatial as well as temporal variation in the (estimated) R number across Wales during our study window, with little detailed data on the accuracy of these estimates. Although difficult to justify incorporation of such estimates into formal models, we will use what is known to inform discussion of our results. We will assess if available anonymised residential identifiers allow creation of usable household/residential clusters, and, if so, whether extension to include clustering improves our models. We will consider further use of care home residence identifiers and critical care and hospital in-patient spells in defining potential explanatory covariates and factors for inclusion in models.

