**Methods and analysis:**

This is a quasiexperimental study undertaken in Wales where records for people who were identified for shielding were already anonymously linked into integrated data systems for public health decision-making. We will: interview policy-makers to understand rationale for shielding advice to inform analysis and interpretation of results; use anonymised individual-level data to select people identified for shielding advice in March 2020 and a matched cohort, from routine electronic health data sources, to compare outcomes; survey a stratified random sample of each group about activities and quality of life at 12 months; use routine and newly collected blood data to assess immunity; interview people who were identified for shielding and their carers and NHS staff who delivered healthcare during shielding, to explore compliance and experiences; collect healthcare resource use data to calculate implementation costs and cost–consequences. Our team includes people who were shielding, who used their experience to help design and deliver this study.

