Shielding aimed to protect those judged to be at highest risk of serious harm should they become infected with COVID-19.^5^ The mechanism for avoiding harm was to avoid infection. Clinically extremely vulnerable (CEV) patients with diagnoses including cancer, serious heart conditions, respiratory problems and receiving certain treatments such as transplants and immunosuppressant medications were identified through algorithms and individual clinical screening methods from routine national and local National Health Service (NHS) data sources.^6–8^ Following a refinement of the medical criteria for shielding in May 2020,^9^ the shielding population increased. In England, it was estimated to be 2.2 million and in Wales 133 000 people at July 2020.^10 11^ Shielding in the UK cost £308 million to deliver in the first 4 months.^12^

Shielding is a new intervention, uniquely used in the UK during the 2020 pandemic without prior evidence of effects on health outcomes or behaviour including intended and unintended consequences.^12–16^ The WHO recognises that some people are at higher risk than others from COVID-19, but states that ‘all must act to prevent community spread’.^17^ It encouraged measures—including physical distancing, handwashing and stay-at-home advice—to limit transmission and protect populations to ensure that health services can sustain increased demand for patient care and treatment.

Evidence is now emerging of effects of shielding on: physical and mental health; well-being and quality of life including social isolation, loneliness and anxiety; access to medical care.^18–21^ Higher COVID-19 rates among people who shielded are also reported.^22 23^ There may be additional secondary effects on physical and mental health, across the shielded population or in subgroups such as the very elderly, people in different clinical condition groups and ethnic minorities. Questions remain about whether the screening process, which involved complex stratification based on modelling to account for ethnicity, deprivation and comorbidities, was the most appropriate approach.^5^

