### Participant identification and participation (objectives 2–5)

Eligible participants will include those identified as CEV in Wales between March and May 2020 and who were advised to shield (shielded cohort). We will use individual-level population-scale anonymised data within the Secure Anonymised Information Linkage (SAIL) Databank to identify those shielded and their linked Electronic Health Records (EHR) from routinely collected NHS data sources, Office for National Statistics data and other health and administrative data, including the Wales Multimorbidity Cohort COVID-19 extension, under existing Information Governance Review Panel (IGRP) approvals.^26^ We will also identify a cohort to match those identified for shielding with partners in Digital Health and Care Wales (DHCW), through cohort ‘propensity’ matching variables including age, sex and historic health service utilisation. We will create a stratified random sample from each of the two cohorts for questionnaire distribution and blood sample collection. Prospectively collected data from questionnaires and bloods will be linked back into the SAIL Databank for anonymised linkage. Figure 1 describes data flow. Figure 2 describes recruitment and participation.

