#### Objective 2: effectiveness of shielding

We will create a matched electronic cohort and compare demographics and clinical characteristics to understand differences between the two groups; it will not be possible to achieve a perfect match, but characterisation of differences, incorporated into our statistical analysis plan, will allow appropriate adjustments when answering our research questions. We know that those warranting shielding will have higher utilisation rates. The rationale for matching on healthcare utilisation is to identify people who should have been shielding (but were missed due to initial selection of conditions based on prioritisation for influenza vaccination and/or administrative error) who can be matched on propensity, to create as similar as possible a comparator group (in the absence of randomisation) and use a difference in difference approach to estimate effectiveness, comparing pre intervention and post intervention health service utilisation rates.

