We will use anonymised individual-level linked routinely collected anonymised EHR data to compare outcomes between the two cohorts—COVID-19 infections, deaths, hospitalisations, immunity status, safety and costs up to 12 months. Inclusion of approximately 120 000 people in each cohort—from date of their addition to the shielding list between 23 March and 31 December 2020; and from 23 March 2020 for the matched control groups: with follow-up of outcomes up to 1 year—gives ample power to detect small differences (standardised statistical effects as small as 0.05, 90% power, 5% significance) in outcomes between groups and between most subgroups. For instance, 3%–5% of each cohort will be recorded as belonging to a black, Asian or other minority ethnic group, allowing comparison of outcomes between up to 6000 people per subcohort; larger numbers will be included in clinical subgroups such as cancer, heart disease, diabetes. We recognise it will not be possible to completely mirror the shielded group in our matched cohort. Our statistical analysis plan will incorporate ways of characterising differences and making appropriate adjustments.We will examine self-reported outcomes at 12 months. We will distribute 1333 postal questionnaires (with online response option) (online supplemental appendix 1) to a stratified random sample in each of the shielded and non-shielded (matched) cohorts to achieve 533 responses in each. Questionnaires will include: the health-related quality-of-life measure (SF12);^34^ measures of common mental disorders, anxiety and depression (PHQ9, GAD7);^35 36^ safety concerns and behaviour during COVID-19 lockdown (staying home, isolating—including within home). Our sample size is sufficient to detect an average difference of 2.5 in SF12 component scores (standardised statistical effect 0.2, 90% power, 5% significance). Our Wales NHS partners, who hold contact details of individuals, will send the questionnaires and assign each an anonymised ID number. This will ensure that the research team has no identifying information about participants at any stage of the evaluation.

10.1136/bmjopen-2021-059813.supp1Supplementary data

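### Shielded people enter on a rolling date and controls on one fixed March date, but the plan neither dates control status nor says how a control listed later is handled

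*Protocol article*

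**What the plan says.** **Shielded entry.** The Protocol article gives three windows. The Abstract will "select people identified for shielding advice in March 2020 and a matched cohort". The section on participant identification takes those "identified as CEV in Wales between March and May 2020". The methods for Objective 2 include people "from date of their addition to the shielding list between 23 March and 31 December 2020".

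**Control entry.** The methods for Objective 2 start follow-up "from 23 March 2020 for the matched control groups". The analysis section for Objective 2 gives another date: "Entry dates are based on the date identified as CEV (shielded cohort) or 20 March 2020 (matched cohort".

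**End of follow-up.** The analysis section states that "12-month follow-up data will be censored by death, or known date of migration from Wales". Listing of a control is not named.

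**Source of controls.** The methods for Objective 2 aim to find "people who should have been shielding (but were missed due to initial selection of conditions". The Introduction adds that the list grew: "Following a refinement of the medical criteria for shielding in May 2020", the shielding population increased.

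**Control status.** Table 1 and the methods for Objective 2 call the comparator non-shielded, without a date at which this is judged. Study design limitations declares an intention-to-treat (treatment allocated) principle. It explains this by undelivered letters, advice not followed, and controls who isolated by choice.

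**The concern.** One cohort accrues over time and the other is fixed at the start. Both come from one population, and the controls are sought among people who resemble those on the list. Some of them can be expected to be listed later. The rules for entry and end of follow-up are stated in the article itself, and they do not say where such a person belongs.

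The answer changes the estimate. Left among the controls, these people bring time under shielding advice into the comparator and pull the contrast towards no effect. Removed because they were listed later, they leave a comparator defined by something unknown at entry: those who die before they could be listed stay as control deaths, while those who live to be listed drop out. That makes shielding look more protective than it is. The comparison affected is the study's main effectiveness contrast, and a large cohort reduces neither error.

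**Working it through.** **The plan's own figure.** The methods for Objective 2 claim 90% power at 5% significance for a standardised effect of 0.05 with about 120 000 per cohort. Two-sided, n per group = 2 × (1.960 + 1.282)² / 0.05² = 8406, far below 120 000, so the claim holds for the whole cohorts. The issue is bias, not power.

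**Does *not listed at entry* define the controls?** With a 20 March start, no one has yet been listed, because the first listing date given is 23 March; the condition excludes nobody. With a 23 March start it can exclude only people listed that day. So *non-shielded* must either refer to later listing or leave later-listed people among the controls.

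**Time left after listing (365 days of follow-up).**

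| Control start | Listed on | Days waited | Days left | Share left (s) |
|---|---|---|---|---|
| 23 March | 31 May | 69 | 296 | 81% |
| 23 March | 31 December | 283 | 82 | 22% |
| 20 March | 31 May | 72 | 293 | 80% |
| 20 March | 31 December | 286 | 79 | 22% |

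**Inputs that the documents do not give.** Let f be the share of controls later listed. It is assumed to be 1% to 20%, all listed on 31 May or all on 31 December, from a 23 March start.

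**Reading A: later-listed people stay as controls.** Attenuation of the contrast = f × s.

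**Reading B: controls are people never listed.** Take f as the share who would be listed if alive, w = 1 − s as the share of the year spent waiting, and the same constant, low death rate in everyone. Deaths kept are proportional to (1 − f) + f × w. Person-time kept is close to (1 − f). Control-rate inflation = [1 − f × (1 − w)] / (1 − f) − 1.

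| f | A, 31 May | A, 31 Dec | B, 31 May | B, 31 Dec |
|---|---|---|---|---|
| 1% | 0.8% | 0.2% | 0.2% | 0.8% |
| 5% | 4.1% | 1.1% | 1.0% | 4.1% |
| 10% | 8.1% | 2.2% | 2.1% | 8.6% |
| 20% | 16.2% | 4.5% | 4.7% | 19.4% |

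Low corner of A: 0.01 × 82/365 = 0.0022. High corner of A: 0.20 × 296/365 = 0.162. High corner of B: (1 − 0.20 × 82/365) / 0.80 = 0.955 / 0.80 = 1.194.

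Under A, an effect of 0.05 becomes 0.0499 (0.05 × 0.9978) at the low corner and 0.0419 (0.05 × 0.838) at the high one. Power with 120 000 per cohort stays near 100%.

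Reading B's arithmetic is for death, which prevents later listing. A non-fatal event does not prevent it and might prompt it, so the formula does not settle the direction for infections or admissions.

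**Scale of the upper end.** 20% of 120 000 controls is 24 000 people, or 18% of the 133 000 that the Introduction gives for the whole Welsh list at July 2020 (24 000 / 133 000). It marks the edge of the illustration and is not an estimate.

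**The case against.** The strongest reply is that the comparator is called non-shielded and treated as a separate cohort, so listed people are plainly meant to be kept out. A control judged in March and analysed as allocated would also fit the declared intention-to-treat principle, and dilution is the known, conservative price of that principle. A condensed article may leave the handling of people who change status to the statistical analysis plan.

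Part of this stands. The label does imply some exclusion, and an as-allocated analysis is a legitimate choice that should be kept. The size may also be small.

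It does not settle the matter. On the stated dates, a March judgement excludes almost no one. Keeping the cohorts disjoint while late-listed people enter the shielded cohort requires knowing who will be listed. The intention-to-treat passage deals with adherence and voluntary isolation, not with a control who is formally given the intervention. The entry dates and ends of follow-up are fixed in the article, so the gap is not only one of detail left to another document.

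A reader might go further and infer that nothing makes a control ineligible, that the same people are certainly counted in both cohorts, and that the contrast is therefore biased. The documents do not support that. Double membership depends on how *non-shielded* is read and on which window applies: a control listed in June 2020 would qualify for the shielded cohort under the December window but not under the March or March-to-May windows.

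**Conclusion.** The point holds as a defect in the definition of the comparator. Shielded entry is rolling, with three different windows. Control entry is fixed, with two different dates. Neither the date of control status nor the handling of later listing is stated. The readings examined lead either to dilution, with possible overlap between the cohorts, or to selection on future status, and these errors run in different directions.

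The size cannot be fixed from the documents. The ranges above, 0.2% to 16% for attenuation and 0.2% to 19% for control-rate inflation, rest on an assumed 1% to 20% of controls later listed on a single date and, for the second range, on equal and low death rates. If few controls were listed later, the effect is negligible. The number can be counted from the list before analysis.

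**What to change.** 1. Reconcile the three shielded entry windows and the two control start dates.
2. Give each control the index date of the matched shielded person. Require that the control is not on the Shielded Persons List on that date, and set no condition on later listing.
3. Allow no one concurrent person-time in both cohorts. In an as-allocated analysis the person stays where first placed. In an analysis that handles later listing, control time stops at listing and any shielded time starts there.
4. Report the number and timing of later-listed controls.
5. Present both the as-allocated analysis and one that handles later listing, either with listing as a time-varying exposure or with censoring at listing plus weighting. Plain censoring is not enough, because listing may follow worsening health and would then remove sicker controls.

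**Cost.** The wording change is small, and listing dates are already needed to define shielded entry. Matching on index dates means some re-matching work, and the second analysis loses some control person-time.

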#### Objective 3: impact of immunological status on outcomes in the shielded population

The majority of people in shielded groups had FBCs and LFTs in recent years. The all-Wales Results Reporting Service data that contain all laboratory tests on the entire population of Wales flow into the SAIL Databank and the Medical Research Council (MRC)-funded ConCOV population cohort (controlling COVID-19 through enhanced population surveillance and intervention project).^8^

These widely collected data will allow an initial broad immunological analysis of humoral immunity (using calculated globulin), cellular immunity (using lymphocyte counts) and impact due to neutropenia (neutrophil counts).

To analyse immunological data we will first plot calculated globulin from low to high in g/L increments against infection, hospitalisation, death and the same analysis for lymphocytes and neutrophils 0.1, 0.2 upwards. Using primary and secondary care data we will define groups within the shielded population, into those with none, or frequent infections to assess whether prior infection frequency relates to outcomes during the pandemic. From the dried blood sample, we will undertake COVID-19 antibody assays, which may include testing for the receptor-binding domain of the spike protein and for nucleocapsid. We will measure T-cell responses to SARS-CoV-2 using a commercially available whole-blood assay (ImmunoServ).^43^ Briefly, this means 10 mL venous blood samples are collected into sodium heparin vacutainers (BD) and stimulated with a SARS-CoV-2 peptide pool containing peptides spanning the entire spike (S1 and S2) protein, nucleocapsid phosphoprotein and membrane glycoprotein for 20–24 hours at 37°C prior to a 2 min centrifugation at ×3000g. The plasma from the top of each blood sample will be harvested and analysed for interferon gamma by ELISA. This will determine levels of T-cell immunity among participants who show no antibodies to COVID-19, even though they have had either natural COVID-19 infection or vaccination to COVID-19. A positive SARS-CoV-2-specific T-cell response will be defined as >23.55 pg/mL IFNg and 50% above the negative (unstimulated) control value, as previously determined in healthy donors.^43^ Tests will be run on the day of sample receipt to avoid deterioration.

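### Calculated globulin, the plan's first measure of humoral immunity, also counts monoclonal protein, so risk in the middle and high bins of the globulin plot could not be attributed to humoral immunity unless those people are flagged

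*Protocol article*

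**What the plan says.** The protocol article covers this in two places, both headed Objective 3.

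Under Methods for each objective, the list of immunological data includes "calculated globulin (total protein—albumin) Laboratory Information Management System (LIMS) test code B3062", with a note that there will be "analysis by low and high calculated globulin". The same list contains "IgG, IgA and IgM LIMS test code B3054" and "Serum electrophoresis".

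Under Analysis, the routine blood results are said to support an "initial broad immunological analysis of humoral immunity (using calculated globulin", with lymphocyte and neutrophil counts serving for the other components. The first analytic step is then fixed: "we will first plot calculated globulin from low to high in g/L increments against infection, hospitalisation, death". Neither the immunoglobulin results nor electrophoresis is given a role in that plot.

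The Introduction describes the shielded population as "Clinically extremely vulnerable (CEV) patients with diagnoses including cancer, serious heart conditions, respiratory problems", among others. It names cancer in general. Blood cancer and monoclonal protein are not mentioned anywhere in the article.

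**The concern.** A marker plotted on one ordered scale should move in the same direction as the thing it stands for. Calculated globulin need not. It is a remainder, everything in total protein that is not albumin, and monoclonal protein is part of that remainder. A rise in monoclonal protein can offset or outweigh a fall in normal immunoglobulin, so a person with poor humoral immunity can be plotted alongside, or above, people whose humoral immunity is intact.

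What is at stake is how the middle and upper parts of the curve are read. If outcomes are worse there, the plot alone cannot tell whether this reflects something about humoral immunity or the presence of people with a monoclonal protein and the disease behind it. More data would not resolve this, because the ambiguity lies in the definition of the marker and not in sampling error.

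**Working it through.** The plan states no figure for this analysis, so there is nothing to reproduce. The check uses the plan's own definition, split into components.

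**Identity.** Calculated globulin = total protein − albumin = G + N + M, where G is non-immunoglobulin globulins, N is normal immunoglobulin and M is monoclonal protein.

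**Inputs.** The definition comes from the Objective 3 data list under Methods for each objective. The documents give no concentrations, so all of these are assumptions, shown as ranges:

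- G: 16 to 20 g/L
- N, undepleted: 10 to 12 g/L
- N, depleted: 2 to 4 g/L
- M: 0, 5, 10 or 20 g/L

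**Results** (lowest and highest sum over the ranges):

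| Person | Sum | Calculated globulin (g/L) |
|---|---|---|
| Undepleted, M = 0 | 16 + 10 to 20 + 12 | 26 to 32 |
| Depleted, M = 0 | 16 + 2 to 20 + 4 | 18 to 24 |
| Depleted, M = 5 | 16 + 2 + 5 to 20 + 4 + 5 | 23 to 29 |
| Depleted, M = 10 | 16 + 2 + 10 to 20 + 4 + 10 | 28 to 34 |
| Depleted, M = 20 | 16 + 2 + 20 to 20 + 4 + 20 | 38 to 44 |

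**Crossing point.** For two people with the same G, the depleted person ranks above the undepleted one when M exceeds the immunoglobulin deficit, N(undepleted) − N(depleted). The smallest deficit is 10 − 4 = 6 g/L and the largest is 12 − 2 = 10 g/L. With M = 20 g/L, the depleted person ranks 20 − 10 = 10 to 20 − 6 = 14 g/L higher.

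**Reading.** The second row shows the marker working as intended: depletion without monoclonal protein lands at the low end. With M = 5 the depleted person moves up into range of the undepleted group. With M = 10 the two overlap or have crossed. With M = 20 the depleted person lies above the whole undepleted range. The misplacement therefore needs a sizeable monoclonal protein.

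**How many.** The article gives no distribution of calculated globulin, no count of people with a monoclonal protein and no breakdown of the cancer group. The number affected, and its share of any g/L bin, cannot be worked out.

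**The case against.** The strongest reply is that the article makes no false statement. It calls the analysis initial and broad, says the plot comes first, plans to look at both low and high globulin, and already lists the two kinds of test that would sort the problem out. How those tests are used could be set in the full protocol or the analysis plan, neither of which is shown. A plot in g/L steps imposes no straight line, so excess risk at the upper end would be visible.

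Much of this stands, and it rules out several stronger readings that a reader might infer:

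- That the plan treats high globulin as high immunity. No section says so; the article only orders the axis and names the construct.
- That antibody-depleted blood-cancer patients in general are misplaced. Only those with enough monoclonal protein are.
- That the relation between humoral immunity and outcome would be reversed. The low bins do not contain people with a large monoclonal protein, so the low end stays usable.
- That the cancer subgroup in Table 1 is hit hardest. That output concerns COVID-19 antigen and antibody tests, and no globulin plot within cancer is described.
- That a few such people dominate the top bins, or that the cohort is enriched for them. No counts support either statement.

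The reply does not remove the point itself. The article goes beyond leaving detail open: it fixes the marker, the construct it stands for, the scale, the order and the outcomes. On those terms, an excess of events at the upper end would be seen but could not be explained.

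**Conclusion.** The point holds in a limited form. By the article's own definition, monoclonal protein is counted within the measure of humoral immunity. Some people with depleted normal immunoglobulin and a sizeable monoclonal protein would sit in the middle or high bins, and risk seen in those bins could not be attributed to humoral immunity. The threshold of 6 to 10 g/L and the displacement of 10 to 14 g/L at 20 g/L of monoclonal protein rest entirely on the assumed concentrations; the direction follows from the definition alone.

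The consequence is confined to one exploratory step of Objective 3. The comparison of outcomes between the shielded and matched cohorts does not use this plot and is not affected.

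**What to change.** Add a few sentences to the Objective 3 analysis, applied before the globulin plots are drawn:

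1. Flag people with a known monoclonal protein, using the serum electrophoresis results already listed and diagnosis codes where available.
2. Show the main globulin curve without the flagged people, plot them separately, and report how many there are.
3. Where IgG, IgA and IgM were measured in people without a flag, check that calculated globulin tracks them.
4. State that high calculated globulin will not be interpreted as intact or greater humoral immunity.

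The cost is one extra flag, mostly from data the study already plans to hold, and a short addition to the text. The downsides are a small loss of people from the main curve and incomplete detection: electrophoresis may not have been done in everyone, so some monoclonal proteins will stay unrecognised. Step 4 is needed for that reason even after the flag is applied.
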